### Nested qualitative study

Trial participants will be purposively selected for qualitative interviews after completing the 6-month outcome assessments. The aim of the qualitative study is to explore the trial participants’ perceptions of the intervention, the quality of the care received, their satisfaction with the peer, and the impact of their health problems on themselves and their children. We expect 40 women to be approached for IDIs, which will continue until data saturation is reached. These interviews will include trial participants from both intervention and control arms, women who withdraw from the trial, participants who recover and those who remain depressed at the final end-point assessment. Apart from the trial participants, we will also conduct IDIs with peers and health system personnel to take their views and perceptions about the linkage and task-sharing aspects of the intervention. All interviews will be audio recorded and transcribed. Analysis will be done manually using a thematic framework approach. The qualitative team will be separate to the intervention and outcome assessment teams.

### Data management

Baseline and follow-up outcome data will be captured electronically using tablet computers. In addition, process data from peers will be collected. Baseline and outcome data will be remotely uploaded as a CSV (comma-separated values) file to the main data server, which will run the software programs STAR and ODK in India and Pakistan, respectively. Both files will be compliant with good clinical practices (including a date and time stamp of original data entry and with an audit trail to document any subsequent changes). Process data will be collected in paper form, and this will be manually entered and stored as CSV files using the same data collection platform. THPP quality-related data will also be collected in paper form. All data, range and consistency checks will be performed at weekly intervals separately for each data source. Any queries identified will be resolved promptly by the data management team, and the database will be updated, maintaining the audit trail. All types of data will be kept in separate databases and only merged into a master database after data collection is completed and each individual database is locked. Access to the data will be protected by password at multiple levels and no member of the trial team apart from the data managers will have access to these passwords. The database will be backed up daily, with off-site storage on external hard drives and DVD media.

Qualitative data will be collected using digital recorders together with written field notes and memos. The former will be transcribed in the language of the interview, anonymised but linked with the trial ID and translated for analysis. A similar procedure will be followed for the written data. Digital recordings will be stored in a secure, password-protected folder.

### Analysis

The quantitative analysis will be done using STATA (version 13) following CONSORT guidelines for individually randomised and cluster-randomised trials respectively. Flow charts will include the number of participants seen at each stage of the trial, including the number screened, eligible, randomised and analysed for the primary outcome. Initial analyses will compare baseline characteristics of enrolled participants by arm and follow-up status. The outcome measures will be summarised at baseline and the 3- and 6-month postnatal follow-ups by intervention arm, summarised by means (standard deviation), medians (interquartile range) or numbers and proportions as appropriate (and including age, gender and baseline outcome score). For continuous outcomes, histograms within each arm will be plotted to assess how closely the scales follow a normal distribution to determine how to describe the outcomes and how to do the inferential analysis properly.

The primary analyses will be ITT at the 6-month follow-up visit adjusted for the baseline measure of the outcome. In the Pakistan trial, mixed-effects logistic regression models will be used to analyse binary outcomes, adjusting for village clusters as random-effects variables and Union Councils as fixed effects. In the Indian trial, peers will be adjusted for as a random effect in the analysis. Analyses of continuous outcomes will use mixed-effects linear regression, additionally adjusting for the baseline value of the outcome. Adjustments will also be made for variables for which randomisation did not achieve a balance between the two arms at baseline.

Effect sizes will be reported as: (1) crude and adjusted relative risks estimated using the marginal standardisation technique with 95 % confidence intervals for the ratios estimated via the delta method [46] for binary outcomes, (2) and as mean differences and standardised mean differences, with 95 % confidence intervals for continuous outcomes. Missing data for the outcomes will be estimated using multiple imputation [47]. Secondary analyses will include repeated measures analyses of data collected at the 3- and 6-month postnatal follow-ups, which is efficient use of all available data.

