#### SHARE Pakistan

The power calculations assume the following:That 40 village clusters are randomised with a 1:1 allocation ratio, stratified within 11 union councils (i.e. a stratified cluster randomised trial).Intra-cluster correlation (ICC) of 0.07 in the intervention arm, and 0.05 in the control arm, to allow for between-village cluster correlation. This is a conservative estimate based on the Rahman et al. THP trial [22] in a similar population, where ICC of 0.04–0.09 was observed between union councils (which were the cluster units). We would expect a substantially lower ICC between villages within a union council.That 14 participants are recruited per village cluster, with loss to follow-up of 20 % over 6 months (conservative, based on the Rahman et al. trial, which had 10 % loss to follow-up of mothers at 6 months) [22].

The sample size of 560 participants recruited provides 90 % power to detect a difference in remission at 6 months of 65 % in the intervention arm and 45 % in the control arm. This sample size also provides 90 % power to detect an effect size of 0.4 for the continuous outcomes.

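### Pakistan remission: a mixed logistic model with delta-method intervals on 40 villages and 11 fixed union councils gives about 10% type I error at the planning ICCs if fitted by maximum likelihood; for PHQ-9 severity the method is left open

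*Protocol article*

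**What the plan says.** The design is given under Power calculations, SHARE Pakistan: "40 village clusters are randomised with a 1:1 allocation ratio, stratified within 11 union councils". The planning values there are "Intra-cluster correlation (ICC) of 0.07 in the intervention arm, and 0.05 in the control arm", and "14 participants are recruited per village cluster, with loss to follow-up of 20 % over 6 months". The same paragraph calls the ICCs conservative because they come from variation between union councils, and adds: "We would expect a substantially lower ICC between villages within a union council".

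The Analysis section specifies mixed-effects logistic regression for binary outcomes, "adjusting for village clusters as random-effects variables and Union Councils as fixed effects". Results are reported as relative risks by marginal standardisation, with 95% "confidence intervals for the ratios estimated via the delta method". Continuous outcomes get mixed-effects linear regression with 95% intervals. For these, the text does not say whether the fit is by maximum likelihood or REML, or which reference distribution applies. It mentions no small-sample correction for either type of outcome.

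**The concern.** The delta-method interval is a large-sample device, and here the treatment effect is estimated between villages. Twelve village-level coefficients (11 councils and arm) are fitted to 40 villages. Two errors then push in the same direction.

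- Maximum likelihood estimates the between-village variation as if no degrees of freedom had been spent on the councils and arm. In effect it divides by 40 rather than 28, so the standard error is too small.
- A normal critical value of 1.96 is used where t on 28 df would be the reference.

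The first error is the larger one. At stake are the false-positive rate and interval coverage for the primary 6-month comparison. An error rate of 10% means that a nominal 95% interval for remission covers about 90% of the time.

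**Working it through.** **Inputs from the protocol:** 40 villages, 1:1, 11 union councils; 14 women per village with 20% loss, so 14 x 0.8 = 11.2 analysed per village and 20 x 11.2 = 224 per arm; ICC 0.07 and 0.05; remission of "65 % in the intervention arm and 45 % in the control arm", and 38% against 22% (Table 4); "an effect size of 0.4 for the continuous outcomes". **Assumptions:** two-sided 5% level, inferred from the 95% intervals; the number of villages per council, which the protocol does not give.

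**Step 1. Reproduce the stated power.** The design effects are 1 + 10.2 x 0.07 = 1.714 and 1 + 10.2 x 0.05 = 1.510. For 65% against 45%, the variance is (0.2275 x 1.714 + 0.2475 x 1.510)/224 = 0.00341, the SE is 0.0584 and the ratio is 0.20/0.0584 = 3.43. The other two outcomes follow in the same way.

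| Reference | 65% v 45% | 38% v 22% | Effect size 0.4 |
|---|---|---|---|
| Stated (Table 4) | 90% | 81% | 90% |
| Normal | 92.9% | 83.7% | 91.5% |
| One village per arm removed | 91.6% | 81.8% | 90.1% |
| Noncentral t, 28 df | 91.1% | 81.0% | 89.6% |

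The last two rows match the stated figures to within 2 points.

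**Step 2. Mechanism.** Take unit total variance and the mean planning ICC, 0.06. A village mean has variance 0.06 + 0.94/11.2 = 0.144. Maximum likelihood centres on (28/40) x 0.144 = 0.101. Subtracting the within-village part, 0.084, leaves about 0.017 for the between-village variance, against a true 0.06 (slightly more once negative values are set to zero). In this balanced approximation the estimate is zero when a chi-square on 28 df falls below 40 x 0.084/0.144 = 23.3, which happens in about 28% of trials.

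If the variance were never cut off at zero, the type I error would be 2P(t28 > 1.96 x sqrt(28/40)) = 2P(t28 > 1.64) = 11.2%. With an unbiased variance and z it would be 2P(t28 > 1.96) = 6.0%. Cutting off at zero pulls the first figure down, more so at low ICCs.

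**Step 3. Simulation under no effect, z reference, nominal 5%.** The analysed number per village is Binomial(14, 0.8). The logistic model used 2,500 runs per setting, remission 45% in both arms, and seven councils of 4 villages with four of 3. The linear model used 4,000 runs per setting with that layout and also with nine councils of 4 and two of 2. The Monte Carlo SE is about 0.3 to 0.6 points.

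| ICC | Logistic, ML, delta-method RR | Linear, ML | Linear, REML |
|---|---|---|---|
| 0.07/0.05 | 9.9% | 10.3-10.5% | 6.0-6.2% |
| 0.05 | 9.6% | 9.1-9.9% | 5.4% |
| 0.02 | 7.4% | 7.6-8.5% | 5.1-5.8% |
| 0 | 5.3% | 5.2-5.5% | 4.2-4.6% |

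A separate logistic simulation (2,000 runs per setting, 50% remission, the second layout, Wald test) gave 9.0%, 10.7% and 7.1% in the first three rows.

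**Step 4. What restores 5%.** Changing only the reference to t on 28 df while keeping maximum likelihood is not enough: at ICC 0.05 to 0.07 the logistic model still gives 8.2-8.4% and the linear model 7.7-9.3%. REML with t on 28 df gives 4.4-5.3% for the linear model. A village-level analysis with t on 28 df gives about 4-6%.

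**The case against.** A reader might infer that both primary outcomes are tested at about twice the nominal rate whatever is done. The document does not support that, for three reasons.

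- **Estimator.** The text never names maximum likelihood, and it ties the delta method only to relative risks. For PHQ-9 severity, REML is not excluded, and REML with z gives only about 6% at the planning ICCs. The estimator and degrees of freedom are also details that an analysis plan, not shown here, commonly settles. This stands: for severity the point is an ambiguity to close, not a stated error. It stands less well for remission, where both the model and a large-sample interval are named, and maximum likelihood is the ordinary way to fit such a model.
- **ICC.** With councils as fixed effects, the within-council ICC drives the error, and the protocol expects it to be substantially lower than the planning values. This stands as a limit on size. It does not remove the point: inflation is still about 7% at 0.02, and an analysis should hold its error rate at the values on which the trial was powered.
- **Simulated model.** The planned analysis also adjusts for baseline and for imbalanced covariates, and uses multiple imputation; none of these was simulated. The figures are therefore indicative.

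**Conclusion.** The concern holds in conditional form. For remission, the stated model and interval method, fitted by maximum likelihood, give about 10% type I error at the planning ICCs of 0.05 to 0.07, about 7% at 0.02 and about 5% at 0. For PHQ-9 severity the result depends on a choice that the text leaves open: maximum likelihood with z gives about 9-11% at the planning ICCs and about 5-8.5% at ICC 0 to 0.02, while REML with z gives about 6% at the planning ICCs. A general doubling of the error rate for both primary outcomes is not shown.

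The conclusion rests on an assumed layout of villages per council (the linear results barely changed between two layouts), a two-sided 5% level, remission near one half, and models without covariates or imputation. It is worth correcting because it affects the primary comparison, the error favours finding an effect, and the remedy is cheap.

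**What to change.** **Continuous outcomes.** State that the mixed linear model is fitted by REML, with t-based tests and intervals on about 28 df (Satterthwaite, Kenward-Roger or between-within).

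**Binary outcomes.** Replace the Wald test and the normal delta-method interval with a small-sample method whose estimate and interval come from the same analysis. Either of these would do:

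- A village-level analysis of covariate-adjusted summaries, with baseline PHQ-9 among the covariates, adjusted for union council and referred to t on 28 df. The relative risk and its interval are both taken from this analysis.
- A permutation test of arm within union councils, with the interval obtained by inverting the test.

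Keeping the marginally standardised relative risk as the estimate while borrowing an interval from a village-level analysis is best avoided, because the two need not agree. Changing only the critical value to t on 28 df would leave about 8% for remission at the planning ICCs.

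**Cost.** A sentence or two in the Analysis section and a little more analysis work. The sample size need not change: t on 28 df gives about 91%, 81% and 90% power against the stated 90%, 81% and 90%.

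### The core primary model is fixed in advance, but added covariates depend on observed baseline imbalance, and the method for PHQ-9 severity is left open to by-arm histograms

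*Protocol article*

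**What the plan says.** All the analysis text is in the Analysis section of the protocol article.

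- **Fixed core.** "The primary analyses will be ITT at the 6-month follow-up visit adjusted for the baseline measure of the outcome". For Pakistan, "mixed-effects logistic regression models will be used to analyse binary outcomes, adjusting for village clusters as random-effects variables and Union Councils as fixed effects". For India, peers enter as a random effect. For continuous outcomes, "Analyses of continuous outcomes will use mixed-effects linear regression, additionally adjusting for the baseline value of the outcome".
- **Added covariates.** In the same paragraph as the primary analysis: "Adjustments will also be made for variables for which randomisation did not achieve a balance between the two arms at baseline". No list, threshold or test follows, and nothing limits the adjustment to a sensitivity analysis.
- **Choice of method.** One paragraph earlier: "For continuous outcomes, histograms within each arm will be plotted to assess how closely the scales follow a normal distribution", and the purpose is "to determine how to describe the outcomes and how to do the inferential analysis properly". No criterion and no alternative method is named, and nothing says that the check is blind to arm.
- **Reporting.** Both crude and adjusted relative risks will be given. Neither is called primary.

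The Abstract names two primary outcomes at 6 months: remission (binary) and severity (continuous). Baseline assessments lists eight items. The two SHARE India sections, under Design and under Randomisation, stratify by urban or rural residence because pilot data showed that depression prevalence differed between them. The India model in Analysis does not name that stratum, whereas the Pakistan model does name union council.

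**The concern.** Two stated rules let data seen by arm shape the primary analysis.

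The first admits covariates because they differ between arms, not because they predict outcome. Under randomisation such differences are mostly chance, so chance and an unstated threshold decide which covariates enter. A prognostic variable that happens to be balanced stays out, and the precision it would have given is lost.

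The second rule is the more serious, because it uses outcome data by arm. A reader cannot tell whether the severity result will come from the stated linear mixed model or from something else chosen after the histograms have been seen. A switch to a rank-based method, for example, would also change what is estimated, although the plan says it will report mean differences.

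What is at stake is the credibility of the reported intervals. If several versions of the primary result are permissible, the interval from the chosen one does not reflect that choice.

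**Working it through.** **1. The plan's own power figures (Table 4).** Two-sided alpha of 0.05 is assumed, since none is stated.

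Pakistan:
- Women followed per village: m = 14 × 0.8 = 11.2. Per arm: 20 × 11.2 = 224.
- Design effects: 1 + 10.2 × 0.07 = 1.714 (intervention) and 1 + 10.2 × 0.05 = 1.51 (control).
- Severity: 0.4 / √[(1.714 + 1.51)/224] = 3.33, and Φ(3.33 − 1.96) = 91.5% (stated 90%).
- Remission at the two cut-offs, cluster-level t with 38 df: 91.6% and 81.8% (stated 90% and 81%).

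India:
- Per arm: 140 × 0.85 = 119. With 30 peers, m = 119/30 = 3.97.
- Design effect, intervention arm only: 1 + 2.97 × 0.05 = 1.148.
- Severity: 0.4 / √[(1.148 + 1)/119] = 2.98, and Φ(2.98 − 1.96) = 84.5% (stated 84%).
- Remission: 86.4% and 74.7% (stated 86% and 74%).

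The table reproduces within 2 points. This point neither disputes nor changes it.

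**2. How often chance changes the model.** Assume eight independent baseline variables and a significance-test trigger α. Then P(at least one flagged) = 1 − (1 − α)^8:

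| Trigger | At least one flagged |
|---|---|
| p<0.05 | 34% |
| p<0.10 | 57% |
| p<0.20 | 83% |

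In Pakistan a check that ignores clustering would flag more. If the baseline variables have an ICC of 0.05 (assumed), the design effect with 14 women per village is 1 + 13 × 0.05 = 1.65. The flag rate per variable is then 2 × [1 − Φ(1.96/√1.65)] = 13%, and at least one of eight is flagged 66% of the time. This ignores any gain from stratification.

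**3. Type I error.** Simulation under no effect, at India's analysed size (238 women). Assumptions: eight covariates with joint R² of 0.05 to 0.40, a skewed outcome, an ordinary linear model, no baseline PHQ-9 and no clustering. There were 6,000 runs per setting.

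| Procedure | Type I error |
|---|---|
| All eight covariates, fixed in advance | 4.9-5.4% |
| Imbalance rule applied mechanically (p<0.05 or p<0.10) | 3.7-4.9% |
| Smallest p over covariate choices | 6.9-8.7% |
| Smaller p of t-test and rank test | 6.3-6.8% |
| Smallest p over both kinds of choice | 8.2-9.8% |

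**4. Power lost by leaving out balanced prognostic variables.** 119 per arm, effect 0.4 SD, baseline PHQ-9 always in the model, p<0.05 flag, no clustering, 4,000 trials per setting. All correlations with outcome are assumed.

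| Each covariate | Baseline PHQ-9 | Flagged only | Always adjusted |
|---|---|---|---|
| 0.10 | 0.3 | 89% | 91% |
| 0.10 | 0.5 | 94% | 96% |
| 0.05 | 0.3 | 89% | 89% |

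The loss is 0 to 2 points. A wider gap, 88% against 96%, appears if each covariate correlates 0.2 with outcome (joint R² = 8 × 0.2² = 0.32) and baseline PHQ-9 is left out of the model.

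**5. India's stratum.** Randomisation stratified on residence tends to balance residence. An imbalance trigger will therefore normally not select it, although the protocol itself gives a reason to regard it as relevant to depression. So the variable the design singles out is the one this rule is least likely to add.

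**The case against.** Several points on the other side stand.

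- Most of the primary model is fixed: intention-to-treat, 6 months, baseline outcome, model form and clustering terms. A reader might infer that the whole primary test is decided after seeing the data by arm. The text does not support that. Only the extra covariates and the method for continuous outcomes are open, and binary remission is untouched by the histogram rule.
- A reader might also infer that imbalance-based adjustment inflates type I error. It uses baseline data, and applied mechanically it is at or slightly below nominal. Inflation needs an analyst who tries several models and keeps the best, and the protocol describes no such practice.
- The eight-point power gap needs strong covariates and does not represent a model that always contains baseline PHQ-9.
- The histograms can be read as a routine assumption check with linear mixed regression as the default.
- In Pakistan, villages are randomised before women are recruited, and the protocol itself mentions recruitment bias after randomisation. Imbalance there need not be pure chance, so examining it has a rationale.

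The argument that all this belongs to an unseen analysis plan is weaker. The article does not merely omit detail. It states two rules, and an analysis plan that followed them would inherit the problem. As for the assumption-check reading, the text says that the plots settle "how to do the inferential analysis properly", which goes beyond a check on a settled model.

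**Conclusion.** The point holds in limited form. The protocol fixes the core primary model, but it leaves the added covariates to an undefined imbalance trigger. It also leaves the method for one primary outcome, PHQ-9 severity, to by-arm outcome plots, in tension with its own statement that linear mixed regression will be used.

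The harm is discretion and a model partly set by chance, not a built-in false-positive excess. The 34% to 83% range rests on eight independent variables and on triggers that the protocol does not state. The figure of about 7-10% type I error applies only if the most favourable model is picked. The loss of 0 to 2 power points rests on modest assumed correlations and would be larger with stronger covariates. Clustering was not simulated, and Pakistan's cluster design was not simulated at all. No sample size or stated power figure changes. The change should be made, since it costs little and forestalls a foreseeable challenge to both trials.

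**What to change.** Before unblinding, in the protocol or analysis plan:

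1. Fix the primary models as arm, baseline PHQ-9, the stratification factor (union council in Pakistan, as already stated; add urban/rural residence in India), the stated clustering terms, and a short named list of prognostic baseline variables already collected.
2. Make imbalance-triggered adjustment a labelled sensitivity analysis in both trials, with imbalance defined. In Pakistan this still addresses imbalance that may arise from recruitment after randomisation.
3. Fix mixed-effects linear regression as the primary analysis of PHQ-9 severity, with a prespecified robust or bootstrap check.
4. Do any check of distributions on pooled data, blind to arm.
5. State that the adjusted estimate is primary and the crude one supportive.

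The cost is a few sentences. It needs no new data, no extra participants and no change to the sample size.
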